**Figure 1 fig1:**
[figure not shown]
CONSORT study flow diagram of the present protocol; CONSORT, Consolidated Standards of Reporting.

Phase 2 will be a full-scaled trial with an additional third arm (1:1:1 allocation) as a non-treatment, standard-of-care group, with refinements and power analysis based on Phase 1 results.

### Procedures

For both groups, 8 weekly sessions will be delivered remotely on Microsoft Teams by licensed therapists (e.g., Psychologist, Occupational Therapist) with mental health experience; discipline experts will also deliver content for the Education and Self Management Strategies Group. Sessions will last 1.5 h, with 10–15 patients per group (factoring in attrition).

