### Aims and hypotheses

In sum, while management of acute COVID is being studied extensively, there is no candidate treatment that targets, let alone alleviates, all or most symptoms of PASC across patients. In response to this gap in care, we developed an education and strategies intervention inspired by findings in related populations that have shown efficacy. This intervention synthesized by psychiatrists and clinical psychologists provides practical recommendations to manage both the specific and non-specific symptoms of PASC. The current study aims to (i) demonstrate the feasibility and efficacy of a novel education and strategies intervention for self-management of PASC symptoms that can be delivered cost-effectively, (ii) and to disseminate an intervention package to aid symptom self-management free-of-charge to licensed therapists for delivery to their patients with PASC. The intervention package will be fully manualized, with (i) videos of presentations from clinician-scientists (cardiology, neurology, respirology, rheumatology, psychology) with experience in PASC that includes frequently asked questions from patients and answers from clinicians; and (ii) PowerPoint presentations plus scripts to be delivered by the facilitator.

The treatment under development employs remote delivery, which has shown to be cost-effective (74, 75), and can tackle the scale and geographic distance of patients from treatment centers. Remote delivery also prevents infection risk, employing a group-based approach which has shown to be cost-effective (76), and may be psychologically optimal given the proliferation of online groups for individuals with PASC, suggesting a need for mutual support. Importantly, group-based approaches for related disorders have been proven effective and feasible (77) as have telerehabilitation and education approaches (78).

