### Study design

The Phase 1 trial is a block randomized, controlled, parallel group, two arm, assessor-blinded trial with a 1:1 allocation. Participants will be randomly assigned to either the Education and Self-Management Strategies or the Mindfulness Skills groups. The allocation sequence is determined using the random function in Microsoft Excel by the study coordinators prior to recruitment. The study coordinators will screen, consent, enroll, and assign participants to their study identity numbers. Qualitative assessment of *N* = 20 patients from the Education and Self-Management group will be purposively (i.e., subjectively) sampled to attain a heterogeneous subset of patients. Qualitative information will be combined with quantitative to permit a more thorough understanding of the outcomes and to aid in further program refinement before undertaking the Phase 2 full-scale RCT. This study design is summarized in COSORT flow diagram presented in Figure 1.

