#### Efficacy analyzes

To assess pre-to post-treatment and follow-up changes for the primary outcome (PMCSMS), we will undertake repeated measures group (Education vs. Mindfulness) by time (pre-, post-, and follow-up-education/mindfulness/waitlist group). ANCOVAs controlling for acute COVID-19 severity and time post-diagnosis. Secondary outcomes will also be examined in the same manner.

Hierarchical regression analyzes will be performed to examine impact of potential moderator variables on pre-to-post treatment improvement on the PMCSMS. In the first block, the moderators will be age, acute COVID severity, and time-post diagnosis. Sex and gender will be included in the second block, and Brief COPE, AIIR and MHLC will be added in the final block. Analyzes of repeated measures data will be performed using the Mixed Models for Repeated Measures (MMRM) methodology (96). We will employ a comparison of bias-corrected covariance estimators for MMRM analysis in longitudinal data with dropouts in order to accommodate the possibility of missing assessments or of assessments at different times post-diagnoses and to provide an effective framework for hierarchical regression analyzes and further exploratory analyzes (96).

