Hence, the study stands to reduce the suffering and improve the quality of life of patients with PASC. Recognizing the unique and diverse nature of symptoms, the strategies and education intervention protocol incorporates a combination of educational modules, teaching of practical strategies, interactive question and answer period and peer support, to empower participants with knowledge, skills, and a robust support system. Educational presentations are tailored to provide insights into the varied symptoms and their management, fostering a proactive approach to healthcare. A question-and-answer period ensures that individuals receive guidance specific to their experiences, promoting a targeted and effective self-management strategy. Peer support, on the other hand, creates a community where shared experiences foster mutual understanding and encouragement. The ultimate goal is to enhance the overall quality of life for participants by mitigating symptom burden and intrusiveness, improving coping mechanisms, and fostering confidence to self-manage. We anticipate that a well-rounded approach to self-management will not only alleviate symptoms but also positively impact mental health, thereby contributing to an improved quality of life. Moreover, the intervention may also help to reduce the impact of PASC on the healthcare system by empowering participants to manage their condition independently and helping patients to discern when to seek out physician support for symptoms and when to self-manage. This, in turn, may alleviate the burden on healthcare resources while offering individuals a sense of control and agency over their health. Through these interventions, our study aspires to bridge existing gaps in Long COVID care and contribute meaningful insights to the broader field of chronic illness management.

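### Both arms are treated in therapy groups of 10–15, but the stated efficacy model and sample size allow for no correlation within a therapy group

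*Protocol article*

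**What the plan says.** Under Study design, Phase 1 is a "block randomized, controlled, parallel group, two arm, assessor-blinded trial with a 1:1 allocation"; participants are assigned individually. Under Procedures, "For both groups, 8 weekly sessions will be delivered remotely on Microsoft Teams by licensed therapists", "with 10–15 patients per group (factoring in attrition". The group setting is meant to be active: the Discussion says of the Education intervention that peer support "creates a community where shared experiences foster mutual understanding and encouragement". Table 1 and the text around it give that arm a question-and-answer period in each session. The Mindfulness protocol has participants discuss the previous week's experience together.

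Under Efficacy analyzes, the primary outcome (PMCSMS) is assessed by "repeated measures group (Education vs. Mindfulness) by time" "ANCOVAs controlling for acute COVID-19 severity and time post-diagnosis", and secondary outcomes likewise. The section adds: "Analyzes of repeated measures data will be performed using the Mixed Models for Repeated Measures (MMRM) methodology". It also mentions bias-corrected covariance estimators, but ties them to dropout and to missing or differently timed assessments. No therapy-group or therapist term is named.

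Under Participants, the sample size is built from 26 pairs (paired tests, effect size 0.59), 20% attrition and a further 25% for the 1-month follow-up, giving 45 per arm.

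**The concern.** People who sit through eight sessions together, with the same leader and the same discussion, tend to end up more alike than people in different groups. Part of the spread in outcome then lies between therapy groups, and 45 participants in 3 to 5 groups carry less information about the arm than 45 independent participants. A model whose only correlation is within person does not see this, so its between-arm standard error is too small.

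At stake is how Phase 1 is read. Ethics and dissemination makes the larger trial conditional on preliminary efficacy in Phase 1, and Aims and hypotheses bases the Phase 2 power analysis on Phase 1 results. Over-precise between-arm results would make that evidence look firmer than it is, and a Phase 2 calculation without a design effect would be too small.

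**Working it through.** **Inputs.** From the article: 45 per arm, effect size 0.59, 26 pairs, 20% and 25% losses (Participants); therapy groups of m = 10 to 15 (Procedures). Assumed: ICC 0.01 to 0.10, and the unspecified standard alpha and beta read as two-sided 0.05 and 80% power.

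**1. The article's own figure.** A paired t-test with d = 0.59 needs 25 pairs; the stated 26 gives 82.4% power. Adding losses: 26/0.8 = 32.5, rounded up to 33, and 33/0.75 = 44; unrounded, 26/(0.8 × 0.75) = 43.3. The stated 45 is therefore explained by independent participants and the two losses alone. What is left over is 45/43.3 = 1.04, smaller than even the smallest design effect below (1.09).

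**2. Number of therapy groups.** 45/15 = 3 and 45/10 = 4.5, so about 3 to 5 per arm.

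**3. Effect of ignoring them.** Design effect DE = 1 + (m − 1) × ICC. The unadjusted standard error is too small by 1 − 1/√DE. The actual two-sided false-positive rate is 2 × [1 − Φ(1.96/√DE)]. The effective number per arm is 45/DE.

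| m | ICC | DE | SE too small by | False-positive rate | Effective n of 45 |
|---|---|---|---|---|---|
| 10 | 0.01 | 1.09 | 4% | 6.0% | 41 |
| 10 | 0.05 | 1.45 | 17% | 10.4% | 31 |
| 10 | 0.10 | 1.90 | 27% | 15.5% | 24 |
| 15 | 0.01 | 1.14 | 6% | 6.6% | 39 |
| 15 | 0.05 | 1.70 | 23% | 13.3% | 26 |
| 15 | 0.10 | 2.40 | 35% | 20.6% | 19 |

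**4. Simulation check** (40,000 trials per setting, two-sample t-test ignoring therapy group, one time point). Rates at ICC 0, 0.01, 0.05 and 0.10:

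- 3 groups of 15 per arm: 5.0%, 6.6%, 13.6%, 21.6%.
- 4 groups of 11–12 per arm: 4.9%, 6.4%, 11.2%, 17.0%.

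With the planned losses, 45 × 0.8 × 0.75 = 27 remain, or 3 groups of 9. The rates are then 6.0%, 9.7% and 15% at ICC 0.01, 0.05 and 0.10. A t-test on therapy-group means held 4.8% to 5.2%.

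**5. Price of the correction.** With 3 groups per arm, a comparison of group means has 2 × 3 − 2 = 4 degrees of freedom (critical value 2.78), against 88 (1.99) when therapy group is ignored. For an illustrative between-arm effect of 0.59 and 3 groups of 15, power is about 51% at ICC 0.01 and 37% at 0.05. The unadjusted test shows 78% and 74%, but at an inflated error rate. The article's 0.59 comes from paired tests, so it is used here only as an illustration.

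**The case against.** The strongest reply is that this is silence in a condensed article: it never says that participants are independent, and random-effects structure is often left to a fuller plan. That stands as a caution. But the article does fix the arm, time and covariate terms and the purpose of its covariance estimators, and it carries out a sample-size calculation that closes without any design effect. Model and sample size omit the therapy group in the same way.

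Several stronger readings are tempting and are not supported.

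- *A reader might infer that the error rate is known to be far above 5%.* No ICC is given. At 0.01 the excess is small; only at assumed values of 0.05 to 0.10 is it large. The figures are also for a single-time-point comparison, not the planned covariate-adjusted model.
- *A reader might infer that Phase 2 will inherit a too-small standard error.* The article takes an effect size from Phase 1. A standardised effect rests on the between-person standard deviation, which clustering barely changes. The Phase 2 risk is a missing design effect in a calculation not yet written.
- *A reader might list peer support, calendar time and therapist as shared in every group.* Peer support is described only for Education. If the arms run concurrently, calendar effects largely cancel from the contrast. The article does not say whether therapists differ between groups; if one led every group in an arm, therapist would be confounded with arm and no random effect would remove it.
- *A reader might treat a false positive here as fatal.* Phase 1 is for feasibility and effect size, and no significance threshold for proceeding is stated.

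It is also true that a random group effect is poorly estimated here. In simulation with 3 groups of 15 per arm, its variance was estimated as zero in 51% of trials at ICC 0.01 and 31% at 0.05. Depending on the degrees of freedom used in those cases, the size at ICC 0.01 was 3.6% or 0.7%. This shapes the fix but does not justify ignoring the therapy group.

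**Conclusion.** The point holds conditionally. Followed as written, the between-arm analysis understates uncertainty for any positive within-group correlation that arises during treatment. The direction does not depend on the ICC; the size does. Under assumed ICCs of 0.01 to 0.10 and therapy groups of 10–15, the false-positive rate is roughly 6–7% to 15–21% instead of 5%, and 45 participants per arm are worth about 41 down to 19. A positive ICC is plausible because both arms work through shared sessions, but the documents do not establish its value. Severity: should-fix.

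**What to change.** 1. Record therapy group and therapist for every participant.
2. Add a therapy-group random effect, nested in arm, to the primary and secondary models. It must act on the post-baseline visits or on baseline-adjusted outcomes, because a group effect constant over all visits would cancel from the arm-by-time contrast. Use small-sample degrees of freedom based on the number of groups (Kenward-Roger or Satterthwaite), say what is done when the variance estimate is zero, and keep the term whatever its estimated size.
3. Give a baseline-adjusted comparison of therapy-group means as a check.
4. Present Phase 1 between-arm results as estimates with these wider intervals, and report the ICC with its uncertainty.
5. For Phase 2, apply the design effect over a range of ICCs, since 3 to 5 groups per arm cannot pin one down. Use a partially nested model, because the no-treatment arm is not grouped.

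Treatment is unchanged, and the only added data are the group and therapist identifiers. The real cost is precision: wider intervals, few degrees of freedom and the loss of power shown above.

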#### Education and Self-Management group protocol

All 8 sessions include education and independently deployable practical strategies (e.g., energy conservation, mindfulness and Cognitive Behavioral Therapy) and principles of self-compassion; self-care, cued diaphragmatic breathing, and phased return to physical activity that will be practiced during and between sessions. While the literature reveals that PASC symptoms can have specific aetiologies, the diagnosis of the etiology of a given symptom in a given patient may be uncertain. Moreover, the presence of some PASC symptoms may cause or exacerbate other symptoms (e.g., fatigue may result in or worsen attentional difficulties). Therefore, the education and strategies we provide are intended to be useful whether or not we have certainty of the underlying symptom cause in any given patient. Restated, the focus is on providing education and strategies for ameliorating symptoms, without making any assumptions about the cause of symptoms in any individual patient.

Benefits of this type of protocol (i.e., strategies and education) include non-invasiveness and no financial cost to patients. This is important given growing concern that in the absence of treatment for the wide-ranging symptoms of PASC, pernicious treatments (80–83) may fill the void.

Each session will end with a question-and-answer period. The content presented in each week is outlined in Table 1. During weeks 3–6, medical experts will deliver a 20–25-min presentation on their respective area of expertise and its relationship to Long-COVID, and provide self-management strategies.

**Table 1 tab1:** Overview of Education and Self-Management Strategies group protocol content.

Week	Topic	Subject expert(s)
1	Overview & Introduction	Psychologist
2	Intro to self-management strategies: discuss the importance of self-care/self-management of symptoms in recovery (e.g., Goal Setting, Energy Conservation, Managing Fatigue, Activity Scheduling, Sleep and Exercise/Nutrition)	Psychologist
3	Respiratory symptoms: presentation on the topic of long-term respiratory symptoms associated with COVID, recommendation of at-home breathing strategies and exercises (e.g., diaphragmatic breathing, active cycle breathing), discussion and question and answer period	Respirologist & Physiotherapist
4	Cardiac symptoms: presentation on the topic of persistent post-COVID heart-related symptoms and disorders, recommendation of a safe and gradual approach to returning to physical activity, potential role for multidisciplinary rehabilitation, when to see a specialist, discussion and question and answer period	Cardiologist
5	Rheumatological symptoms: presentation on the long-term rheumatological symptoms after COVID, discussion of recommended pharmacological and non-pharmacological self-management strategies focusing on (i) pain and inflammation control, and (ii) maintenance of physical function/avoidance of long-term deformities, question and answer period	Rheumatologist
6	Neurological & Mental Health Symptoms: overview of Long-COVID neurological and mental health symptoms, discussion of biological and environmental factors that can impact symptoms, recommendation of self-management strategies (patient organizations, exercise, socialization, self-compassion), question and answer period	Neurologist & Psychologist
7	Cognitive symptoms: presentation of cognitive symptoms associated with Long COVID, discussion of self-management strategies such as checking the basics (e.g., sleep, diet, physical exercise), incorporating concepts of neuroplasticity and environmental enrichment in daily life, question and answer period	Psychologist
8	Wrap up and review of clinical recommendations, self-management and self-care strategies	Psychologist

This table describes the structure and main focus of each session in the 8 week Education and Self-Management Strategies intervention, which are led by psychologists and other medical experts.

#### Mindfulness skills group protocol

The Mindfulness Skills intervention is an 8-week program designed to provide an introduction to basic mindfulness skills. Each session begins with a brief breath focus practice followed by discussion of the participants’ experience from the previous week. Each session also includes some didactics on a new related mindfulness skill that is introduced and practiced, followed by a question and answer period. Topics covered include breath focus practices, modes of being: autopilot vs. awareness, body scan practice, cognitive distancing strategies, and building a sustainable mindfulness practice. The content covered each week is outlined in Table 2.

**Table 2 tab2:** Overview of mindfulness group protocol content.

Week	Topic	Subject expert
1	Overview & Introduction	Psychologist
2	Two modes of being: Autopilot vs. Awareness; Exercise – Two ways of knowing (from Mindful Way -think about your feet vs. directly sense your feet – to help people understand the difference); Breath Focus practice; Mindfulness of everyday activities discussion	Psychologist
3	Introduction to the Body Scan; Body Scan practice/discussion	Psychologist
4	Using mindfulness responsively – introduce/practice Short Breathing Space (STOP – notice); Compassionate Body Scan practice/discussion	Psychologist
5	Mindfulness of Breath, Body, Sounds, Thoughts, and Choiceless Awareness	Psychologist
6	Review of cognitive distancing strategies/practice; Meditation/discussion – Loving Kindness for Ourselves	Psychologist
7	Review of cognitive distancing strategies/practice; Meditation/discussion – working with difficulty (from Mindful Way)	Psychologist
8	Building a Sustainable Mindfulness Practice; Guest House Poem – discussion Meditation – Compassionate Friend – Neff/Germer	Psychologist

This table describes the structure and main focus of each session in the 8 week psychologist-led mindfulness program.

### Outcome measures

After providing informed consent to participate in the study and prior to commencing the intervention groups, participants will be asked to complete an online background questionnaire in order to assess potential moderators. This background questionnaire collects demographic information (e.g., age race, sex, gender, highest education, occupation), previous and current medical and psychiatric history, current symptoms and healthcare supports.

#### Feasibility measures (Education and Self-Management group only; Objective 1)

(i)Recruitment (percentage of eligible participants that consented); retention (percentage of consented participants that completed the study); and adherence rates (percentage of sessions attended and outcome measures completed)(ii)Standard Session Feedback Form: this 5-item patient reported outcome measure (PROM) was created by our group, and uses a 5 point Likert scale to measure the utility of content/strategies, amount of content, barriers to application, and any changes/benefits noticed from applying the strategies.(iii)Exit interview: a semi-structured, qualitative interview comprising open-ended questions followed by probes. The interview probes pros/cons of intervention design and impact of the intervention on health and symptom self-management. Probes are based on the Workgroup for Intervention Development and Evaluation Research (WIDER) recommendations regarding content, format, delivery, timing issues and personnel (84). The interview will also contain probes for impact on health, health-related actions, including self-management of Long-COVID symptoms and health care visits.

#### Efficacy measures (Objective 2)

All primary and secondary outcomes are PROMs. Table 3 summarizes the timeline of the outcome measure collection.

(i)Primary outcome:

Perceived Medical Condition Self-Management Scale (85) (PMCSMS). An 8 item tool using a 6-point scale to measure confidence to self-manage symptoms, with strong validity and reliability (85, 86), and associated with high treatment adherence and beneficial outcomes (85).

(ii)Secondary outcomes:

Utilization of Healthcare Services Questionnaire. This tool was created by our group to measure past and planned healthcare-related visits.Depression, Anxiety and Stress Scale (DASS-21 (87)). A 21-item tool that uses a 4-point scale to measure stress, depression and anxiety symptoms.Quality of Life Enjoyment and Satisfaction Questionnaire – Short Form (Q-LES-Q-SF (88)). A 16-time tool that uses a 5-point scale to measure quality of life and degree of enjoyment and satisfaction experienced by participants in various areas of daily living.Adapted Illness Intrusiveness Rating (AIIR (89, 90)). A 13-item scale using a 7-point scale to measure intrusiveness of symptoms in daily life.Life Orientation Test – Revised (LOT-R) (91). A 10-item tool using a 5-point scale to measure dispositional optimism.International Physical Activity Questionnaire (IPAC) (92). An 8-item tool to measure engagement in physical activity.

(iii)Control/Moderator variables

Brief COPE (93). A 28-item tool using a 4-point scale to measure ways of coping with stress in life.Somatic Symptom Scale – 8 (SSS-8 (94)). An 8-item tool using a 5-point scale to measure of somatic symptom burden.Multi-dimensional Health-Related Locus of Control (MHLC (95)). An 18-item tool to measure the locus of control for health-related behaviors.

**Table 3 tab3:** Summary and timeline of outcome measure collection.

Timeline		Outcome category	Outcome measures
Pre-intervention	Week 0; prior to first session	Feasibility (Objective 1)	Recruitment rate
		Efficacy (Objective 2)	Perceived Medical Condition Self-Management Scale Utilization of Healthcare Services Questionnaire Depression, Anxiety and Stress Scale Quality of Life Enjoyment and Satisfaction Questionnaire – Short Form Adapted Illness Intrusiveness Rating Brief COPE and Life Orientation test Somatic Symptom Scale Multi-dimensional Health-Related Locus of Control International Physical Activity Questionnaire
Intervention	Weeks 1–8	Feasibility (Objective 1)	Retention/adherence rate, Session Feedback Form
Post-intervention	Week 8; last session	Feasibility (Objective 1)	Qualitative exit interview (Education intervention group only)
		Efficacy (Objective 2)	(all efficacy outcomes mentioned above)
1-month follow-up (phase 1 and phase 2)	Week 12	Efficacy (Objective 2)	(all efficacy outcomes mentioned above)
3-month follow-up (phase 2 only)	Week 20	Efficacy (Objective 2)	(all efficacy outcomes mentioned above)

This table describes all the outcome measures and their timeline for administration. COPE: Coping Orientation to Problems Experienced Inventory.

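### Education-only exit interviews, and feedback forms that may also be Education-only, cover the same ground as the self-reported outcomes and risk differential reporting between arms

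*Protocol article*

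**What the plan says.** All references are to the protocol article.

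- **Who is interviewed.** Study design: "Qualitative assessment of *N* = 20 patients from the Education and Self-Management group will be purposively" sampled. Participants gives 45 recruits per arm. Table 3 marks the interview as "Qualitative exit interview (Education intervention group only").
- **What the interview covers.** Feasibility measures: "The interview will also contain probes for impact on health, health-related actions, including self-management of Long-COVID symptoms and health care visits". The same item says it also explores the merits and drawbacks of the intervention's design.
- **The Session Feedback Form.** It has five items, covering "utility of content/strategies, amount of content, barriers to application, and any changes/benefits noticed from applying the strategies". It sits under the heading "Feasibility measures (Education and Self-Management group only; Objective 1"). Table 3 lists it for weeks 1 to 8 as "Retention/adherence rate, Session Feedback Form", with no arm restriction in that row.
- **Timing.** Table 3 puts the interview and all efficacy questionnaires in one block, at week 8 and the last session. The efficacy questionnaires are repeated at week 12. No order within week 8 is given.
- **Outcomes.** Efficacy measures states that every primary and secondary outcome is patient-reported. The primary outcome, PMCSMS, measures confidence in managing one's own symptoms. A secondary questionnaire records past and planned use of health care.
- **Use of the result.** Efficacy analyzes plans an Education versus Mindfulness by time comparison over pre, post and follow-up. Aims and hypotheses says that Phase 1 supplies the effect size and the power analysis for Phase 2, which is purely quantitative.

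**The concern.** In a comparison of two behavioural programmes on self-report, research contact outside the programmes should be the same in both arms. Here it is not. Some Education participants are asked, by a member of the research team, how the programme affected their self-management and their visits. They also rate their self-management and visits on the trial questionnaires, in the same week and again four weeks later. Mindfulness participants have no such interview, and possibly no feedback form.

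Reflecting on the programme, receiving extra attention, or wishing to please the team can change how a person rates their own confidence. Assessor blinding does not help, because the respondent supplies the rating and knows which programme they attended.

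The hypotheses expect Education to do better than Mindfulness on exactly these constructs. If part of an observed difference came from the interview, it could not be separated from the programme effect. It would also not recur in a Phase 2 without interviews, so a power calculation based on it would make Phase 2 too small.

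**Working it through.** **1. The plan's own sample size.** A paired t-test with effect size 0.59, two-sided 5% and 80% power (assumed for the stated standard values) needs 25 pairs; at the stated 26 pairs, power is 0.824. Inflation: 26/(1 − 0.20) = 32.5, rounded to 33, and 33/(1 − 0.25) = 44, against 45 stated. Both agree closely enough and are not in dispute. The implied completers per arm are 45 × 0.80 = 36 at week 8 and 36 × 0.75 = 27 at week 12.

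**2. Overlap of content.**

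| Research procedure | Subject | Outcome on the same subject |
|---|---|---|
| Exit interview | Impact on self-management | PMCSMS (primary) |
| Exit interview | Health care visits | Utilization questionnaire (secondary) |
| Session Feedback Form | Changes or benefits from the strategies | PMCSMS, less directly |

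**3. Timing.** At week 8 the interview can affect the questionnaires only if it comes first, which is not stated. At week 12 the order is fixed: an interview at week 8 precedes the follow-up questionnaires whatever happened within week 8. Week 12 belongs to the planned primary-outcome analysis, and the sample size was inflated for it.

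**4. Share of the arm interviewed.**
- 20/45 = 44.4% of those recruited.
- 20/36 = 55.6% of week-8 completers, if all interviewees complete.
- At week 12, 20/27 = 74.1% if no interviewee is lost. If they are lost at the same 25% rate, 20 × 0.75 = 15 and 15/27 = 55.6%.

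**5. Effect on the contrast.** Shift in the arm contrast = share interviewed × shift per interviewee. The documents give no shift per interviewee, so 0.1, 0.3 and 0.5 SD are assumed. The last columns give the chance of a significant result favouring Education when there is no true difference (two-sample t-test, two-sided 5%, equal variances). Without any shift it is 2.5%.

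| Assumed shift per interviewee | Contrast, 45 per arm | Contrast, 36 per arm | False result for Education, 45 per arm | 36 per arm |
|---|---|---|---|---|
| 0.1 SD | 0.044 | 0.056 | 4.0% | 4.2% |
| 0.3 SD | 0.133 | 0.167 | 9.1% | 10.3% |
| 0.5 SD | 0.222 | 0.278 | 17.9% | 21.3% |

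With 27 per arm and all 20 interviewees retained, the upper bound, the contrast moves by 0.074, 0.222 and 0.370 SD, and the rates are 4.5%, 12.3% and 26.6%. This assumes that the shift persists for four weeks.

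These rates come from a single-time-point comparison, not from the planned repeated-measures model. A downward shift of the same size would move the contrast equally far against Education. If the feedback form is Education-only, any shift it causes applies to the whole arm, so the contrast moves by the full amount.

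**The case against.** The strongest case against has four parts.

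- **Direction.** A reader might infer that these procedures bias the comparison towards Education. The documents do not establish that. The interview also asks about drawbacks and the form about obstacles, and dwelling on those could lower confidence. This stands: only a risk is shown.
- **The form.** A reader might infer that Mindfulness participants never receive it. The only support is the Feasibility measures heading, which is loose: it also covers the recruitment rate, which precedes allocation, and completion of outcome measures, which both arms do. Table 3 attaches the Education-only limit to the interview and not to the form. Use at every session is likewise inferred from the form's name and the weeks 1 to 8 row. This stands: the point about the form is conditional.
- **Order at week 8.** A reader might take the interview's place above the questionnaires in Table 3 as a sequence. It is not one, because the table lists feasibility before efficacy at week 0 too. A condensed article may also leave the order of procedures within a visit to the full protocol. This stands for week 8. It does not answer week 12, where the article's own schedule puts the interview first.
- **Reach and purpose.** Only 20 of 45 are interviewed, and Phase 1 is mainly a feasibility study, for which interviews are needed. Both are true. But Phase 1 is also meant to yield an effect size, and the feasibility aim does not require interviews before the last efficacy measurement.

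**Conclusion.** The point holds as a risk of differential reporting, not as a demonstrated bias. What the article fixes is an Education-only interview, on the subject of the primary outcome and one secondary outcome, scheduled alongside the week-8 questionnaires and before the week-12 questionnaires, with every outcome self-reported. The risk applies at week 12, and at week 8 only if the interview comes first. An upward shift for Education is plausible but not certain.

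The size is unknown. The range of about 0.04 to 0.28 SD in the arm contrast at 45 or 36 per arm rests entirely on assumed shifts of 0.1 to 0.5 SD in all 20 interviewees; the upper figure also needs all of them to be among 36 completers. The consequence that matters most is a Phase 1 effect size containing a component that a Phase 2 without interviews would not reproduce. This is a worthwhile, low-cost improvement and not a flaw that invalidates the trial.

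**What to change.** 1. In Table 3, schedule the exit interview after the week-12 questionnaires. This protects both post-baseline time points.
2. If that is not acceptable, require at the least that the week-8 questionnaires are submitted before any interview. This protects week 8 only.
3. State that the Session Feedback Form goes to both arms with equivalent wording, and make the Feasibility measures heading agree with Table 3.

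An analysis with and without the interviewees is not a substitute. They are a purposive subset of one arm, so leaving them out breaks the randomised comparison and brings in selection.

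Cost: a small change of wording, about four weeks' longer recall for interviewees, and a five-item form in the Mindfulness arm if it is not already used there. No additional participants are needed.
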